## Abstract

**Background:**

Anthracycline-induced cardiac toxicity is a cause of significant morbidity and early mortality in survivors of childhood cancer. Current strategies for predicting which children are at greatest risk for toxicity are imperfect and diagnosis of cardiac injury is usually made relatively late in the natural history of the disease. This study aims to identify genomic, biomarker and imaging parameters that can be used as predictors of risk or aid in the early diagnosis of cardiotoxicity.

**Methods:**

This is a prospective longitudinal cohort study that recruited two cohorts of pediatric cancer patients at six participating centres: (1) an Acute Cohort of children newly diagnosed with cancer prior to starting anthracycline therapy (*n* = 307); and (2) a Survivor Cohort of long-term survivors of childhood cancer with past exposure to anthracycline (*n* = 818). The study team consists of three collaborative cores. The *Genomics Core* is identifying genomic variations in anthracycline metabolism and in myocardial response to injury that predispose children to treatment-related cardiac toxicity. The *Biomarker Core* is identifying existing and novel biomarkers that allow for early diagnosis and prognosis of anthracycline-induced cardiac toxicity. The *﻿Imaging Core* is identifying echocardiographic and cardiac magnetic resonance (CMR) imaging parameters that correspond to early signs of cardiac dysfunction and remodeling and precede global dysfunction and clinical symptoms. The data generated by the cores will be combined to create an integrated *risk-prediction model* aimed at more accurate identification of children who are most susceptible to anthracycline toxicity.

**Discussion:**

We aim to identify genomic risk factors that predict risk for anthracycline cardiotoxicity pre-exposure and imaging and biomarkers that facilitate early diagnosis of cardiac injury. This will facilitate a personalized approach to identifying at-risk children with cancer who may benefit from cardio- protective strategies during therapy, and closer surveillance and earlier initiation of medications to preserve heart function after cancer therapy.

**Trial registration:**

NCT01805778. Registered 28 February 2013; retrospectively registered.

**Electronic supplementary material:**

The online version of this article (doi:10.1186/s12885-017-3505-0) contains supplementary material, which is available to authorized users.

## Background

With contemporary therapies, over 80% of children diagnosed with cancer will become long-term survivors [1, 2]. The childhood cancer survivor (CCS) population in the United States exceeds 390,000 [3]. CCS are at significant risk of serious morbidity and premature mortality as a result of their cancer therapy [4, 5]. Cardiac toxicity, mainly caused by anthracycline chemotherapy agents (e.g. doxorubicin, daunomycin) which are administered to more than 50% of children with cancer [6], is a major cause of this morbidity. Although observed frequencies vary between studies, up to 60% of patients treated with an anthracycline will develop echocardiographic abnormalities [7]. These abnormalities increase over time in incidence and severity in a significant proportion of patients [8–10]. The risk of congestive heart failure (CHF) in children exposed to a cumulative anthracycline dose greater than 300 mg/m^2^ approaches 10% by 20 years after their cancer therapy [11], but even children exposed to lower doses of anthracyclines are at significantly increased risk for CHF [7, 12]. Compared to their siblings, CCSs have a 15-fold increased risk of developing CHF [13]. Cardiac disease is the third leading cause of premature death in CCS (after cancer recurrence and second malignancies), with a 7-fold increased risk of premature cardiac death as compared to the general population. The relative risk of cardiac death remains elevated even in CCS who have survived for more than 25 years after their primary cancer [14].

Clinicians rely on established clinical risk factors (e.g. cumulative anthracycline dose, radiation therapy to a field that involves the heart, younger age at treatment, female gender, longer follow-up, and CHF during therapy [7–9, 15–19]) in order to identify which children treated for cancer are at risk for late-onset cardiac dysfunction. The Children’s Oncology Group guidelines for surveillance for late effects in CCS recommend a surveillance echocardiogram or MUltiGated Acquisition scan (MUGA) every 1, 2, or 5 years depending on three risk factors: (1) age at treatment; (2) cumulative anthracycline dose; and (3) receipt of chest radiation [20–22]. However, these factors are imperfect predictors, and do not take into account individual biological variations in metabolism of chemotherapy and response to cardiac injury. Consequently, their discriminative power for individual patient decision making is poor [23].

Despite the identification of some genetic variants that predispose to anthracycline cardiotoxicity, genetic factors need further study and validation before they can be applied in clinical practice [24]. Different cardiac biomarkers could be used for the detection of subtle cardiac damage prior to the onset of imaging or functional changes, and may identify an “at risk” population that could benefit from modification of future chemotherapy, administration of a cardioprotectant or intervention aimed at the prevention of cardiac remodeling and progressive dysfunction [25]. Further validation of the utility of biomarker testing to predict individual risk of cardiac toxicity is required before it can be recommended for routine use.

Most commonly, cardiotoxicity is monitored using echocardiographic measures of systolic function including left ventricular (LV) ejection fraction (EF) or shortening fraction (SF). These parameters are frequently normal early in the natural history of anthracycline cardiomyopathy, even when biopsy studies demonstrate significant evidence of myocardial damage such as apoptosis and interstitial fibrosis [26]. More recently, novel echocardiographic parameters such as tissue Doppler echocardiography and strain imaging, have been shown in adults to detect early changes in cardiac function prior to changes in ejection fraction. There are still limited data in children on the utility of the new echocardiographic methods [27]. Other novel imaging techniques include the use of Cardiac Magnetic Resonance (CMR). Late gadolinium enhancement (LGE) is commonly used as an imaging biomarker of discrete myocardial scarring in cardiomyopathies [28], although its significance in anthracycline-induced cardiotoxicity is uncertain [29]. Using T1relaxometry based approaches, commonly referred to as ‘T1 mapping’, it is possible to measure myocardial extracellular volume (ECV), which has been shown to correlate with the degree of cardiac fibrosis [30, 31]. ECV has been found to be correlated with cumulative anthracycline dose, exercise capacity and myocardial wall thinning in a group of 30 adolescent patients at least 2 years following anthracycline treatment [32]. If these findings are confirmed and if ECV can be demonstrated to carry prognostic significance, it could serve as an early tissue marker of fibrotic ventricular remodeling, especially if it precedes decreased ejection fraction in children post-anthracycline therapy. Given the limitations of using SF/EF for the early detection of cardiac damage and the observation that CHF may not occur for years (or even decades) after anthracycline exposure, it is not feasible to use SF/EF or clinical cardiac disease as the sole outcome in studies of CCS during the pediatric years. There is a pressing need to develop more sensitive imaging and biomarker techniques that will allow for earlier detection of sub-clinical treatment-induced cardiac toxicity, and that can be combined with genetic predictors to identify survivors at greatest risk for progressive cardiac deterioration [33].

Here we report on the design and methods of the ‘*Novel approaches to the prediction, diagnosis and treatment of cardiac late effects in survivors of childhood cancer*’ study. To our knowledge, this is the first longitudinal pediatric cohort study to evaluate a combination of predictive variables in order to develop a risk prediction algorithm specific to CCS at risk for cardiac disease. We aim to:Identify genetic predictors of anthracycline cardiotoxicity;Assess existing biomarkers and identify novel biomarkers for the assessment of acute and chronic cardiac toxicity in children treated with anthracyclines;Identify the echocardiographic and CMR parameters that best identify early cardiac changes and predict progressive cardiac deterioration after exposure to anthracyclines;Create a statistical model that combines genomic, biomarker, imaging and clinical data to predict which pediatric patients exposed to anthracycline chemotherapy will develop progressive cardiac damage.

## Methods

This is a multi-centre observational cohort study that is being conducted at the Hospital for Sick Children (Toronto, Canada), Princess Margaret Cancer Centre (Toronto, Canada), McMaster Children’s Hospital (Hamilton, Canada), London Health Sciences Centre (London, Canada), The Children’s Hospital of Eastern Ontario (Ottawa, Canada) and The Children’s Hospital of Orange County (Orange County, USA). Ethics approval was obtained by the following Ethics Boards for the conduct of this study: The Hospital for Sick Children Research Ethics Board, University Health Network Research Ethics Board, University of Western Ontario Health Sciences Research Ethics Board, Children’s Hospital of Eastern Ontario Research Ethics Board, McMaster Health Sciences Research Ethics Board, and Children’s Hospital of Orange County In-House Research Ethics Board. Written informed consent was obtained from all study participants (or parent/legal guardian consent along with patient assent, where applicable).

Two patient cohorts were recruited and are being followed longitudinally at the six participating centres.

### Acute cohort

A prospective cohort of patients newly diagnosed with cancer who received anthracycline chemotherapy has been recruited from clinics at the four pediatric participating centres (recruitment target *n* = 270; recruitment actual *n* = 307). We will assess whether genetic predictors of anthracycline susceptibility, biomarkers of early cardiac damage, and imaging parameters of acute cardiac dysfunction predict which patients will demonstrate evidence of persistent or progressive cardiac damage at the 12 months follow-up from their last cycle of anthracycline chemotherapy (See Fig. 1 for timeline of sample and data acquisition in Acute Cohort). Eligibility criteria for both cohorts are provided in Table 1.

**Fig. 1 Fig1:**
[figure not shown]
Data and specimen acquisition from the Acute Cohort. BIOMKR: Serum for biomarkers, ECHO: Echocardiogram, DNA: Blood or saliva for DNA, CLIN: Gather baseline clinical data

**Table 1 Tab1:** Inclusion and exclusion criteria by cohort

	Inclusion criteria	Exclusion criteria
Acute Cohort	1. Aged <18 years at time of cancer diagnosis; 2. Diagnosed with a new malignancy; 3. Cancer treatment plan will require therapy with ≥1 dose of an anthracycline chemotherapy 4. Pre-anthracycline; echocardiograms to occur at the recruiting site; 5. Normal cardiac function prior to the initiation of anthracycline therapy (LVEF >55%).	1. Patients with significant congenital heart defects; 2. Patients who were previously treated with anthracycline chemotherapy or radiation to the chest.
Survivor Cohort	1. Aged <18 years at time of cancer diagnosis; 2. Previously diagnosed with cancer and currently in remission; 3. Patients whose prior treatment plan included therapy with ≥1 dose of anthracycline chemotherapy; 4. Patients who completed their final dose of anthracycline ≥3 years ago; 5. Patients who completed their final dose of a chemotherapy agent other than anthracycline ≥1 year ago; 6. Routinely followed at the recruiting site approximately every 12 months.	1. Prior allogeneic stem cell transplant; 2. Patients with significant congenital heart defects; 3. CMR: general contraindications for a contrast enhanced CMR, and patients who require anaesthesia for MRI (typically <6 years of age) will be excluded.

Family and medical history and demographics are collected at baseline. Data on concomitant medications are collected at each study visit. A blood (4-6 ml) or saliva (2 ml) sample is collected for DNA extraction and genomic analysis. Serial 2D echocardiograms are obtained at baseline, and at 12 months post-final anthracycline therapy dose. Additional echocardiograms are obtained prior to each dose of anthracycline in consenting patients. A blood sample (5-8 ml per time point) is collected prior to each dose of anthracycline therapy, and at 3 months and 12 months post the last anthracycline dose. The consent for biomarker studies is optional. In a subset of patients over 6 years of age, patients are also approached for consent for a cardiac MRI at the 12 month follow-up time point (Table 2).

**Table 2 Tab2:** Schedule of procedures/evaluations in Acute Cohort

Procedure/Evaluation	Baseline (prior to starting anthracycline)	Study Visits prior to each anthracycline dose	3 months after completion of final anthracycline dose (± 4 weeks)	12 months after completion of final anthracycline dose (± 8 weeks)
Informed Consent/Assent	X			
Demographics	X			
Height (cm) & Weight (kg)	X	X	X	X
Concomitant Medications	X	X	X	X
Medical History	X			
Review of Medical Events	X	X	X	X
Cancer Therapy		X	X	
Echocardiogram (ECHO)	X	X^a^		X
Genetic Sample	Obtain one sample at any time point while patient is on-study^%^			
OPTIONAL Biomarker Sample	X	X	X	X

^%^For patients who will be having an allogeneic stem cell transplant, collect the genetic sample prior to the procedure

^a^ECHOs will be performed prior to each dose of anthracycline when possible. If patient/parent is not agreeable to research-only ECHOs, then they will occur only at clinically indicated time points

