### Survivor cohort

The survivor cohort consists of childhood cancer survivors who are three or more years from their last cycle of anthracycline therapy (recruitment target *n* = 920; actual recruitment *n* = 818). This cohort has been recruited from specialized survivor clinics at the six participating centres. A blood or saliva sample for DNA is collected at enrollment. Echocardiogram to assess function and blood sample for biomarkers are obtained at enrollment and annually over 2 years of follow-up (see Fig. 2 for timeline of sample and data acquisition in Survivor Cohort).

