### CORE 1: Genomics

The Genomics Core will perform a comprehensive genome-wide search to identify genes associated with anthracycline cardiotoxicity.

The study will use a nested case-control approach. Patients who are anthracycline sensitive (i.e. develop cardiac dysfunction despite low anthracycline doses), and those who are anthracycline resistant (i.e. have preserved cardiac function despite high anthracycline doses) will be included in a discovery cohort. These patients will undergo whole exome sequencing to identify genes associated with cardiotoxicity. Genes in pathways related to anthracycline absorption, distribution, metabolism, and excretion, and genes important in cardiac response to injury will be prioritized in the analysis. Non-genetic risk predictors will be included in the regression model. The top-ranked genes that are enriched for variants and are deemed biologically relevant will undergo targeted sequencing in the remainder of the cohort which will serve as a replication cohort.

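### Table 2 lets the Acute Cohort's only DNA sample be drawn while tumour cells circulate, so tumour variants can be read as germline in the Genomics Core

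*Protocol article*

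**What the plan says.** The Acute Cohort enrols children at diagnosis, before anthracycline. Table 1 sets no limit on cancer type beyond "Diagnosed with a new malignancy", so haematological cancers are eligible. The text under Table 1 gives the DNA source: "A blood (4-6 ml) or saliva (2 ml) sample is collected for DNA extraction and genomic analysis". It does not tie the source to the diagnosis.

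Table 2 fixes the timing: "Obtain one sample at any time point while patient is on-study". Its footnote adds one restriction: "For patients who will be having an allogeneic stem cell transplant, collect the genetic sample prior to the procedure".

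Survivor Cohort patients must be "Previously diagnosed with cancer and currently in remission", and a prior allogeneic transplant excludes them.

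The Genomics Core section builds a discovery set from patients with dysfunction at low anthracycline doses and patients with preserved function at high doses. It states: "These patients will undergo whole exome sequencing to identify genes associated with cardiotoxicity". Genes enriched for variants and judged biologically relevant go to targeted sequencing in the rest of the cohort. The section on the risk prediction model lists genomics among the candidate predictors for the Acute Cohort.

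**The concern.** The genomic aim concerns inherited susceptibility, so the sample must represent the patient's germline. The transplant footnote shows that the authors considered whose DNA a sample contains, but the rule guards only against donor cells. In untreated leukaemia, or lymphoma that has reached marrow or blood, the nucleated cells in a blood sample can be largely tumour. Saliva also carries white cells, so it reduces the problem without removing it.

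Two errors can follow. Somatic variants can be called as germline, and true germline heterozygotes can be miscalled where the tumour has lost one copy. If affected samples are spread unevenly between the groups being compared, the errors become apparent associations. Otherwise they add noise and reduce power. With one sample per patient, they cannot be reliably repaired afterwards.

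**Working it through.** The article gives no power, effect size or error rate for the Genomics Core, so there is no stated figure to reproduce. Three checks follow.

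**1. What one affected sample looks like.** Let *f* be the share of nucleated cells that are tumour (assumed).

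- Clonal heterozygous somatic variant: allele fraction = *f*/2.
- Germline heterozygote where the tumour has lost one copy: retained allele = 1/(2 − *f*), lost allele = (1 − *f*)/(2 − *f*).

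| *f* | Somatic heterozygote | Germline heterozygote, one copy lost |
|---|---|---|
| 0.3 | 0.15 | 0.59 / 0.41 |
| 0.5 | 0.25 | 0.67 / 0.33 |
| 0.8 | 0.40 | 0.83 / 0.17 |
| 0.9 | 0.45 | 0.91 / 0.09 |

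The germline reference is 0.50. At high *f* a somatic variant lies close to it, so a filter on allele fraction alone would struggle to separate the two. A germline heterozygote in a lost region is then at risk of being called homozygous.

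**2. How many patients could be affected.** The Acute Cohort gives "recruitment actual *n* = 307" and the Survivor Cohort "actual recruitment *n* = 818".

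- Total: 307 + 818 = 1,125. Acute share: 307/1,125 = 27.3%. Survivor share, in remission: 72.7%.
- Exposed = 307 × leukaemia share × share of those sampled before remission. Neither share is in the article; the assumed ranges are 20–50% and 10–100%.
- Low end: 307 × 0.20 × 0.10 = 6 patients (2% of the Acute Cohort, 0.5% of both cohorts).
- High end: 307 × 0.50 × 1.00 = 154 patients (50% and 13.6%).

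**3. What it could do to a gene-burden comparison.** Assume a 5% true carrier rate in both groups, a share *c* of affected samples in each group, and a somatic carrier rate *s* for the gene in those samples. The observed carrier rate is 0.05 + 0.95 × *c* × *s*. The last column is the chance of a result in the direction of the contamination; with no contamination it is 0.025.

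| Per group | *c*, the two groups | *s* | Observed rates | Rejection |
|---|---|---|---|---|
| 100 | 2% / 0% | 2% to 25% | 0.0504 to 0.0548 / 0.05 | 0.026 to 0.035 |
| 100 | 10% / 2% | 10% | 0.0595 / 0.0519 | 0.042 |
| 50 | 25% / 5% | 25% | 0.1094 / 0.0619 | 0.132 |
| 100 | 25% / 5% | 25% | 0.1094 / 0.0619 | 0.223 |

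Every input in this table is an assumption. The effect runs from negligible to material.

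**Could the groups be unbalanced?** The Cardiac Imaging Core section (Aim 1) says anthracycline administration varies with the cancer treatment protocol, so an uneven mix of diagnoses between dose-defined groups is plausible. There is a second route. Under Study outcomes, only the Acute Cohort can become a case through a fall of at least 1 SD in a wall-thickness or thickness-to-dimension z-score from baseline. The two cohorts may therefore contribute cases at different rates, and only one of them can hold pre-remission samples.

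**The case against.** A reader might infer that tumour variants do enter the exome data and gather in one dose group because diagnosis determines dose. The documents do not support that. They give no leukaemia share, no sampling dates and no dose by diagnosis. They also do not say that sites usually draw DNA at baseline: Table 2 leaves the visit open, and Fig. 1, which carries the timeline, is not shown. The direction of any bias cannot be derived. All of this stands.

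Safeguards also stand in part. Most enrolled patients are survivors in remission, and the article does not say how many of the discovery set come from the Acute Cohort. Genes for anthracycline handling and cardiac injury response are prioritised, non-genetic predictors enter the model, and hits go to replication. A false gene would need somatic variants that recur in such a gene and fall unevenly between the groups. However, Acute Cohort patients in the replication set are sampled under the same rule, and the Acute Cohort risk model has no survivors to dilute the problem.

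Finally, a condensed article may leave specimen handling and variant filtering to a laboratory manual or analysis plan. Their absence is therefore not criticised here. The point is the rule that Table 2 does state: it has one exception, and it permits an unsuitable sample.

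**Conclusion.** The concern holds as a weakness in a stated rule. Table 2 permits a pre-remission sample in leukaemia, or in lymphoma with marrow or blood involvement, and such a sample can present tumour variants and copy losses as germline. The allele-fraction results follow directly once a blast fraction is assumed. The number exposed (6 to 154 of 307) and the illustrative rejection rate (0.026 to 0.223 against 0.025) rest on assumed leukaemia share, sampling time, carrier rates and group sizes, so they show a range and not an estimate. Only the Acute Cohort is open to the problem. Because size and direction are unknown and a remedy is cheap, this is a should-fix point and not a fatal one.

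**What to change.** Change the genetic-sample entry in Table 2. In leukaemia, or lymphoma with marrow or blood involvement, draw the DNA sample after documented remission and before any allogeneic transplant, at an existing pre-dose, 3-month or 12-month visit.

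Recruitment is reported as complete, so new wording cannot govern samples already drawn. For those:

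- Check sample date, source and disease status before sequencing.
- Where the sample is pre-remission, redraw at a remaining visit or leave it out of exome discovery.
- Repeat the genomic part of the Acute Cohort risk model without pre-remission samples.

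The cost is a wording change, a check of sample records, and a repeat 4–6 ml blood or 2 ml saliva sample for affected patients still in follow-up. The downside is that a few patients who never reach remission, or who have left follow-up, will have no usable DNA, which makes the genomic sample slightly smaller and conditional on remission. A patient who dies before remission would have no 12-month outcome either, so that loss does not fall on the primary outcome analysis.
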